## Abstract

**Introduction:**

Despite the fact that immobilisation is a major contributor to morbidity and mortality, patients hospitalised in general internal medicine (GIM) wards spend up to 50% of time in bed. Previous studies in selected patient populations showed increased mobility after implementation of goal-directed mobilisation (GDM). Due to the study design used so far, the degree of evidence is generally low. The effect of GDM on clinical outcomes and economically relevant indicators in patients hospitalised in GIM wards is currently unknown. This study aims to evaluate a GDM intervention compared to standard care on physical activity (de Morton Mobility Index, DEMMI) in medical inpatients.

**Methods and analysis:**

GoMob-in is a randomised, controlled, open-label study with blinded outcome assessment. We plan to enrol 160 inpatients with indication for physiotherapy on GIM wards of a tertiary hospital in Bern, Switzerland. Adult patients newly hospitalised on GIM wards will be included in the study. The primary outcome will be the change in the DEMMI score between baseline and 5 days. Secondary outcomes are change of DEMMI (inclusion to hospital discharge), mobilisation time (inclusion to day 5, inclusion to discharge), in-hospital delirium episodes, number of in-hospital falls, length of stay, number of falls within 3 months, number of re-hospitalisations and all-cause mortality within 3 months, change in independence during activities of daily living, concerns of falling, and quality of life within 3 months and destination after 3 months. Patients in the intervention group will be attributed a regularly updated individual mobility goal level made visible for all stakeholders and get a short educational intervention on GDM.

**Ethics and dissemination:**

This study has been approved by the responsible Ethics Board (Ethikkommission Bern/2020–02305). Written informed consent will be obtained from participants before study inclusion. Results will be published in open access policy peer-reviewed journals.

**Trial registration number:**

NCT04760392.

Strengths and limitations of this studyThis is the first study evaluating goal-directed mobilisation in hospitalised general internal medicine patients using blinded outcome assessment.The primary endpoint physical activity will be assessed by change in the de Morton Mobility Index score between baseline and day 5, a reliable tool without floor or ceiling effects.Activity will be recorded by an accelerometer to record the effect of the intervention.The study will also assess independence during activities of daily living, quality of life, number of rehospitalisations and all-cause mortality at 3 months follow-up.The study design is limited by the fact that blinding is not feasible for the interventions and some outcomes.

## Introduction

Decreased mobility during hospitalisation is associated with muscle loss, risk of falls, delirium, functional decline and an increased mortality, especially in the elderly.^1–4^ Bedrest of 10 days in healthy elderly resulted in a substantial loss of muscle strength, power, aerobic capacity and a reduction in physical activity.^5^ Evidence suggests that interventions that promote early mobility have the potential to decrease the risk of falls,^6 7^ to reduce functional decline during hospitalisation,^8^ to shorten duration of delirium^9^ and to reduce the median length of hospital stay (LOS) and mortality.^9 10^ Therefore, early mobilisation is recommended in most patients to prevent functional decline and frailty.^11 12^ Despite recommendations to mobilise patients early, a low level of physical activity is still common and many patients spend most of the time in bed during hospitalisation, irrespective of patient age.^3 12–14^ In a recent Dutch study, inpatients spent almost half of the time in bed and were active only 10% of the time.^15^ Most studies assessing interventions on mobilisation focused on selected patients such as older adults or those admitted to intensive care units. Further, most studies failed to monitor mobility or long-term functional outcomes or had a retrospective design.^2 12 16–18^

Implementation of early mobilisation in general internal medicine (GIM) remains challenging and staff resources-demanding, because mobilisation is usually supervised by healthcare professionals such as physiotherapists. Individual goal-achievement strategies have the potential to complement physiotherapy in rehabilitation.^12 19^ Thereby, a mobility goal is generally defined depending on the individual potential of the patient and communicated to the interprofessional team caring for the patient. Goal-directed mobility (GDM) programmes in GIM showed in temporal cohorts a reduction in LOS and a decrease of falls.^20 21^ Most evidence stems from studies which usually integrated several other organisational changes or were non-randomised trials, for example, implementation of a mobility scale and corresponding mobility goal in hospital wards.^22^ However, pre-post settings do not consider general trends, for example, reduction in LOS and comparators may differ significantly. In one randomised controlled trial, a mobility programme using goal-setting reduced the decline in activities of daily living during acute hospitalisation.^7^ However, it included only a small number of older veterans was labour intense and lacked long-term follow-up.^7^

Due to the low number of studies of limited methodological quality, the level of evidence is low and the impact of GDM on clinical and economic outcomes in GIM patients is widely unknown.^23^

Therefore, this study aims to evaluate a standardised GDM programme in acutely hospitalised medical inpatients on functional capacity during hospitalisation and up to 3 months after study inclusion. All patients will receive physiotherapy treatment as indicated by the physician in charge. Compared with a control group with standard care, patients in the intervention group will receive additional instructions for GDM, physiotherapists will work with goal-setting and the goal will be indicated for all stakeholders at the bedside.

## Methods and analysis

The methods reporting of this randomised trial will follow the recommendations of the SPIRIT statement (table 1).^24^

**Table 1 T1:** Trial registration data

Data category	Information
Primary registry and trial identifying number	ClinicalTrials.gov NCT04760392
Date of registration in primary registry	18 February 2021
Secondary numbers	SNCTP000004280, BASEC2020-02305
Source(s) of monetary or material support	Swiss Society of General Internal Medicine (SGAIM) Foundation, Bern, Switzerland Fondation Sana, Bern, Switzerland
Primary sponsor	Swiss Society of General Internal Medicine (SGAIM) Foundation, Bern, Switzerland (grant number: not applicable)
Secondary sponsor	Fondation Sana, Bern, Switzerland (grant number GF 2021–0048)
Contact for public queries	[name] [contact]
Contact for scientific queries	[name] Department of General Internal Medicine, Inselspital, Bern University Hospital, Bern, Switzerland
Public title	Goal-directed mobilisation of medical inpatients—a randomised, controlled trial (GoMob-in trial)
Scientific title	Goal-directed mobilisation of medical inpatients—a randomised, controlled trial (GoMob-in trial)
Study setting	Number of study centre(s): 1 Type of study centre(s): University Hospital, Department of General Internal Medicine Location, Country: Bern, Switzerland
Health condition(s) or problem(s) studied	Inpatient mobility
Intervention(s)	Intervention group: goal-directed mobilisation
	Control group: standard of care
Key inclusion and exclusion criteria	Ages eligible for study: 18 years or older Sexes eligible for study: both Accepts healthy volunteers: no
	Inclusion criteria: acute hospitalisation on the general internal medicine ward, indication for physiotherapy
	Exclusion criteria: inability to follow study procedures and give informed consent themselves, expected hospital stay for <5 days, bedrest, injuries or relevant neurological deficits one or both lower extremities directly impairing walking capacity, terminal illness
Study type	Interventional Allocation: randomised intervention Masking: single blind (primary outcome assessor) Primary purpose: prevention
Date of first enrolment	14.09.2021
Target sample size	160
Recruitment status	Recruiting
Primary outcome	Change of the de Morton Mobility Index (DEMMI) score between baseline and day 5
Key secondary outcome	Change in DEMMI score between baseline and discharge. Mobilisation time measured by accelerometer between inclusion and day 5. Mobilisation time between inclusion and discharge. Number of delirium episodes. Number of in-hospital falls. Length of hospital stay. Total number of falls (with/without injuries) within 3 months. Number of rehospitalisations and all-cause mortality within 3 months. Independence during activities of daily living: change in Barthel index between study inclusion and 3 months. Change in FES-I between baseline and 3 months. Quality of life: change in EuroQol (EQ-5D-5L) between study inclusion and 3 months. Destination at 3 months after study inclusion (may include: death, acute care hospital, rehabilitation, home, nursing home, others).

DEMMI, de Morton Mobility Index; FES-I, Falls Efficacy Scale-International.

### Study setting

This is an investigator initiated trial. The funder has no role in the study design, the trial oversight, data collection, analysis of the study and publication of the results. The Goal-directed Mobilization of Medical Inpatients (GoMob-in) trial is a pragmatic, randomised, controlled, open-label study with a 3-month follow-up and a blind outcome assessment, being conducted at the Department of General Internal Medicine, Inselspital, Bern University Hospital, Bern, Switzerland.

### Objectives

To evaluate the effect of GDM compared with standard care in hospitalised patients in GIM on physical activity as assessed by the de Morton Mobility Index (DEMMI) score.

### Hypothesis

GDM improves physical activity assessed by DEMMI compared with standard of care in hospitalised patients in GIM.

### Eligibility criteria

#### Inclusion criteria

Subjects fulfilling all of the following inclusion criteria are eligible for the study:

Acute hospitalisation on the GIM ward (elective or urgent admission, at latest on the second day after internal or external hospital admission).Age 18 years or older.Indication for physiotherapy.Informed consent as documented by signature (written informed consent).

#### Exclusion criteria

The presence of any one of the following exclusion criteria will lead to exclusion of the subjects:

Inability to follow study procedures, that is, due to language problems (unable to read, speak or understand German), psychological disorders, severe dementia (defined as to levels 5–7 in the Global Deterioration Scale),^25^ blindness, patients unable to provide informed consent themselves.Expected hospital stay for <5 days.Medically indicated bedrest for more than 24 hours, for example, after surgery.Injuries or relevant neurological deficits one or both lower extremities directly impairing walking capacity (eg, fractures, hemiplegia, previous use of a wheelchair or bedriddenness).Terminal illness (ie, end-of-life care, dying phase).Pregnancy or breast feeding.Previous enrolment in this study.A study participant in the same patient room.Enrolment of the investigator, his/her family members, employees and other dependent persons.

### Estimated sample size and power

The sample size calculation was based on the primary outcome of a clinically meaningful change in the DEMMI score between baseline and 5 days of follow-up. The DEMMI score ranges from 0 to 100 points with 0 indicating no physical activity and 100 indicating maximal physical activity. Based on previous studies on changes in DEMMI scores during short-term hospitalisation of roughly 10 days,^26 27^ we expect a difference in change between the two groups of 5 score points. In an observational study of participants with low and high activity, SD for changes in the DEMMI score was 7.8 and 8.5 points, respectively (personal communication).^26^ In a study on older adult inpatients, the SD was between 12.5 and 15.4 points for absolute DEMMI scores at admission and discharge, respectively.^27^ The SD for changes is typically smaller than for absolute values; we therefore expect a rather conservative SD of about 10 points for the change in our study.

To detect a difference in change of 5 score points with a SD of 10 points, at a two-sided alpha level of 0.05 with a power of 0.8, a sample size of 2×64 participants is required. Based on an estimated drop-out rate of 20%, we aim to include 160 patients into the study (80 in each group).

### Primary outcome

The primary outcome will be the change in physical activity level measured by performance in the DEMMI score between baseline and 5 days of follow-up.^28^ Trained study personnel will evaluate physical activity by using DEMMI score at baseline before randomisation, while a physiotherapist blinded to the group allocation will assess DEMMI score 5 days later.

### Secondary outcome

Change in DEMMI score between baseline at study inclusion and discharge. Patients hospitalised for more than 2 weeks on GIM wards will be assessed on day 14 after study inclusion instead of at hospital discharge.Percentage of time moving between study inclusion and day 5. Activity will be measured using an accelerometer (GENEActiv, Activinsights, Kimbolton, Cambridgeshire, UK) validated to assess activity in the hospital setting.^13 14 29^Percentage of mobilisation time between baseline and discharge or at 14 days (whichever occurs first).Number of in-hospital delirium episodes (follow-up max. 14 days).Number of in-hospital falls (follow-up max. 14 days)LOS defined as days between hospital admission and discharge.Total number of falls (with/without injuries) within 3 months after study inclusion.Number of rehospitalisations and all-cause mortality within 3 months after study inclusion.Change in independence during activities of daily living (Barthel index) between baseline and 3 months after study inclusion.^30 31^Change in Falls Efficacy Scale-International (FES-I) between baseline and 3 months after study inclusion.^32 33^Change in quality of life (EQ-5D-5L) (visual analogue scale (EQ-VAS) and mobility dimension) between baseline and 3 months after study inclusion.^34–36^Discharge destination (death, acute care hospital, rehabilitation, home, nursing home).Reaching the minimal clinically important difference (MCID) of a change in DEMMI score (9 points) between baseline and discharge.^28 37^

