Sociodemographic and anthropometric data (eg, age, gender, weight and height, zip code (rural versus urban living area), marital status, nurse visit at home (German: Spitex), insurance coverage (private or not), admission mode (elective or urgent), transfer from intensive care unit, hospitalisation in the last 6 months), previous use of mobility aids.Comorbidities will be reported by the participant, using an established, systematic method as previously described.^38^Functional status using Barthel index. The Barthel index is one of the most widely used and reliable functional outcome measures and is measured through an established and validated questionnaire where higher scores on a scale between 0 and 100 indicate greater independence in activities of daily living.^30^ It can be conducted by telephone and a validated German version is available.^31^ If the patient is not able to answer the questions, the Barthel index will be administered by interviewing the ward nurse caring for the patient, a family member or any other person caring for the patient before hospitalisation (eg, home care nurse).Concerns of falling using FES-I. FES-I is a validated 16-item tool to evaluate concerns of falling, with 16 score points indicating no concerns of falling and 64 score points indicating high levels of concern.^32^ It can be conducted by telephone and a validated German version is available.^33^Quality of life will be assessed with the EQ-5D-5L questionnaire. The EQ-5D-5L^34 35^ is an established, standardised measure of quality of life consisting of a descriptive system compromising the five dimensions mobility, self-care, usual activities, pain/discomfort and anxiety/depression with five levels each (no problems, slight problems, moderate problems, severe problems, and extreme problems) and a visual analogue scale with 0 indicating the worst health and 100 indicating the best health.^39^ It can be conducted by telephone interview and a validated German version is available.^36^Physical activity will be assessed by a trained study nurse using the DEMMI score. The German version of the DEMMI is a valid^40^ and reliable^39^ instrument to measure physical activity in older adults in the acute hospital setting and has no floor or ceiling effect.^28 37 41^ Based on 15 items (0–19 points with Rasch conversion to a score ranging from 0 (indicating poor physical activity) to 100 (indicating a high level of independent physical activity)), the DEMMI includes evaluation of movement in bed (three items), chair (three), static balance (four), walking (two) and dynamic balance (three). Acute older adult patients with a DEMMI score below 41 score points had significantly lower Barthel index (38% vs 79%), used more mobility aids, were more bedridden, longer hospitalised and were more often discharged to rehabilitation compared with those with a higher DEMMI score.^42^ No association was found for gender, age, weight, body mass index, Charlson comorbidity index or handgrip strength.^42^ Trained personnel is able to complete the DEMMI in no more than 10 min.

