#### Follow-up

Nurses will record falls in the electronic health record (EHR). Hospital parameters, for example, discharge destination, end of hospitalisation, LOS will be collected from the EHR at discharge. Medical data, for example, number of falls and delirium episodes during hospitalisation, main diagnosis and comorbidities will be systematically collected from the discharge letter.

Physical activity will be assessed using DEMMI in all participants on day 5 after study inclusion and on the day of discharge or day 14 (whichever occurs first).

Three months after study inclusion, all participants will be inquired by telephone interview for Barthel index, FES-I, EQ-5D, number of falls since study inclusion (with/without injuries), current destination, rehospitalisations and all-cause mortality. If the patient cannot be reached, a family member or the treating general practitioner will be called to complement data. The patient will be asked to send the falls calendar to the study team. If discrepancy is noted compared with the phone interview, the participant will be called for validation.

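### In-hospital delirium and falls have no stated start, and the whole-stay collection rule lets in events from before randomisation, chiefly for delirium

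*Protocol article*

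**What the plan says.** The Secondary outcome section of the protocol article lists "Number of in-hospital delirium episodes (follow-up max. 14 days" and "Number of in-hospital falls (follow-up max. 14 days". Both lines fix the length of follow-up; neither says when it begins. Table 1 gives no start for them either.

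Other outcomes in the same list do name their start. Falls over the longer period are defined as "Total number of falls (with/without injuries) within 3 months after study inclusion". Length of stay is given a different origin: "LOS defined as days between hospital admission and discharge".

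The Follow-up section gives the collection rule: "number of falls and delirium episodes during hospitalisation, main diagnosis and comorbidities will be systematically collected from the discharge letter". It adds that nurses enter falls in the electronic health record (EHR).

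Table 2 counts its time points from randomisation and places the third visit at discharge or day 14 at the latest. Delirium is read from the EHR at that visit only. In-hospital falls are marked for that visit and also daily.

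Patients can spend time in hospital before they are randomised. The Inclusion criteria allow entry "at latest on the second day after internal or external hospital admission", and the Baseline assessment section records "transfer from intensive care unit" as a patient characteristic.

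**The concern.** An episode that began before allocation cannot have been prevented by goal-directed mobilisation. If it enters the count, it enters both arms alike and hides part of any effect on the ratio scale.

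The outcome line suggests one window and the collection rule another. Someone extracting data from a discharge letter under the rule as written would record every delirium episode of the stay. That includes one that had cleared by the time the patient could consent, since the Exclusion criteria remove only patients unable to consent or follow procedures at inclusion. If the onset date is not captured, the analyst cannot later restrict the count to the intended window.

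Two clinically relevant secondary outcomes are at stake. The primary outcome is not touched.

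**Working it through.** **Which window do the sections imply?**

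| Place in the protocol article | Start | End |
|---|---|---|
| Secondary outcome, delirium and in-hospital falls | not stated; follow-up implies inclusion | 14 days |
| Table 2, third visit | axis runs from randomisation | discharge or day 14 |
| Follow-up, collection from the discharge letter | whole hospitalisation | whole hospitalisation |

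The first two rows agree on inclusion to discharge or day 14. The third is wider at the start, and also at the end for stays beyond day 14.

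**The plan's own figure.** The only computed figure is the sample size for the primary outcome: difference 5, SD 10, two-sided alpha 0.05, power 0.8. The t-test solution is 63.77, so 64 per arm (power 0.801), and 64 / (1 − 0.20) = 80 per arm, 160 in total. It reproduces and has no bearing on this point. No event rate, effect or power is given for delirium or falls, so what follows is conditional on assumptions.

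**Effect on the estimates.** Let each arm have P events before allocation (equal in expectation under randomisation), let the control arm have C events after it, and let the true rate ratio be RR.

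- Absolute difference: (P + C × RR) − (P + C) = −C × (1 − RR). P cancels, so there is no bias.
- Ratio: (P + C × RR) / (P + C) = s + (1 − s) × RR, where s = P / (P + C) is the pre-allocation share of control-arm events. With s > 0 and RR < 1, the ratio moves towards 1.
- If RR = 1, the ratio stays at 1, so type I error is not inflated.

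The Statistical analysis section plans a negative binomial model for counts, which estimates a ratio. It names falls and rehospitalisations as examples; I assume that delirium is treated the same way.

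**Plausible size of s.** Assume a constant daily event rate, 1–2 days in hospital before allocation and 5–14 days after. Then s = days before / (days before + days after).

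| Days before / after | s | True 0.70 seen as | True 0.50 seen as |
|---|---|---|---|
| 1 / 14 | 1/15 = 0.07 | 0.72 | 0.53 |
| 2 / 10 | 2/12 = 0.17 | 0.75 | 0.58 |
| 2 / 8 | 2/10 = 0.20 | 0.76 | 0.60 |
| 2 / 5 | 2/7 = 0.29 | 0.79 | 0.64 |

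**Power.** This uses a Wald test on the Poisson log rate ratio with 80 per arm, a true ratio of 0.50, and an assumed number of post-allocation events per control patient.

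| Events per control patient | s = 0 | s = 0.20 |
|---|---|---|
| 0.1 | 0.20 | 0.17 |
| 0.2 | 0.36 | 0.29 |
| 0.3 | 0.50 | 0.40 |

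Power is low in any case; the dilution lowers it further.

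**The case against.** The strongest reply is that the start is already implied. Elsewhere the article measures follow-up from baseline, the 14-day limit for the DEMMI is tied to study inclusion, and Table 2 runs from randomisation. Where admission is meant as the origin, as for length of stay, the article says so. This stands. A reader might infer that the plan counts pre-allocation events as outcomes, but no section says so. None excludes them either, and the implied window still conflicts with the collection rule.

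Second, falls are recorded daily in the EHR and can probably be placed before or after randomisation. This also stands, so it would be wrong to say that earlier events can never be separated. It helps less for delirium: the EHR is named as a source, but only at the third visit, and no onset date is described.

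Third, the time before allocation is short. Prescreening is confined to the first two days of hospitalisation, and the consent requirement removes many patients with active delirium. A longer intensive care stay before inclusion is possible but nowhere stated. A reader might therefore suppose that a third or a half of counted events predate allocation. Shares of that size exceed the range above, and nothing in the documents supports them.

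Fourth, onset rules and data fields are often left to the full protocol or SAP, which are not shown. The absence of a baseline delirium field from a condensed list is accordingly not the finding. The finding is that the stated collection period does not match the implied outcome window. An SAP can define the window, but it can be applied only if onset was recorded.

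**Conclusion.** The point holds as a mismatch between two sections, not as a rule that earlier events count. The outcome definition leaves the start to inference, and the Follow-up section prescribes a period that includes time before randomisation. It matters mainly for delirium and less for falls.

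The consequence is a rate ratio pulled towards 1 and added noise, with no bias in the absolute difference and no inflation of type I error. With an assumed 7–29% of control-arm events before allocation, a true ratio of 0.70 would appear as 0.72–0.79 and one of 0.50 as 0.53–0.64. These figures rest on a constant event rate and on assumed days before and after allocation, because the documents give no event rates. The primary outcome and the sample size are unaffected. It is a modest problem, worth correcting because the correction is cheap.

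**What to change.** - In Secondary outcome, define both counts as events with onset after randomisation, up to discharge or day 14 after randomisation, whichever comes first. State that an episode already present at randomisation is not an outcome event.
- In Follow-up, replace the whole-hospitalisation period with the same window.
- Record the onset date of each delirium episode.
- Record any delirium or fall between admission and randomisation as a baseline characteristic.

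The cost is a sentence in the outcome definition, a matching change to the collection rule, the onset date, and one extra EHR field at baseline. The drawback is slightly fewer counted events. N = 160 does not change.
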